##### Recommendations (the evidence) being implemented

A review of research evidence was conducted as part of the fourth International Consultation on Incontinence (ICI) [43]. They based their recommendations on gradings derived from the Oxford Centre for Evidence Based Medicine 'Levels of Evidence' [44]. Grading for therapeutic interventions included Grade A: consistent evidence from meta-analysis of trials or good quality RCTs; Grade B: consistent evidence from lower quality RCTs, meta-analysis with homogeneity, good quality prospective cohort studies, good quality retrospective case controls studies, good quality case series; Grade C: expert opinion based on first principles or majority evidence from study types listed in Grade B, or Delphi processed expert opinion. Grade D: no recommendation is possible as evidence is conflicting or expert opinion has not been through a formal analytical process. They note that a Grade A recommendation often means the recommendation is effectively mandatory and placed within a clinical care pathway.

The recommendations to be implemented in this study were thus taken from the algorithm developed by Committee 11 who examined the research relevant to Incontinence in the Frail Elderly [43]. The drafted recommendations were then circulated to continence experts in each country and the continence experts on the study's Advisory Committee. No country-specific issues that may make their implementation problematic were identified by the continence experts. The recommendations [43] to be implemented in the FIRE study are listed below, with their associated level of evidence.

Recommendations to be implemented in FIRE study

1. The patient/resident should be actively screened for urinary incontinence.(Grade A)

2. A detailed assessment should be carried out including:

• Relevant co-morbid conditions should be assessed:

- rectal examination; constipation (Grade C)

- functional assessment (mobility, transfer, dexterity, ability to toilet) (Grade A)

- screen for depression (Grade B)

- assess cognitive status (Grade C)

- any medications that could cause or worsen UI (ICI recommendation)

- any medical conditions that could cause or worsen UI (ICI recommendation)

• Urinalysis should be undertaken (including for haematuria, leucocytes, nitrites) (Grade C)

• Undertake wet checks to assess frequency of urinary incontinence (Grade C)

• Ensure diagnosis of the type of UI is recorded (ICI recommendation):

- Urgency

- Stress

- Mixed

- Other

3. An individualised treatment plan should be in place for:

• Individualised goals of care (Grade C)

• Treatment preferences of resident and/or next of kin (Grade B)

• Bladder retraining (Grade A), or tailored prompted voiding [if able to state name] (Grade A)

• Degree of bother to resident/next of kin of UI (Grade B)

4. Specialist referral should be made if needed (pain, haematuria, UI not classified at urgency, stress or mixed). (ICI recommendation).

##### Ethical Issues

The researchers will adhere to ethical standards for research involving people. In addition, all researchers will abide by their institutional and national ethical requirements. Ethical Committee approval was obtained in England, Sweden, and Republic of Ireland. In the Netherlands, the researchers were advised to get permission from either an ethical committee at site level, or where this did not exist, from a scientific or residents committee at the site. Research Governance approval was also obtained in England, and permission to collect data at the sites obtained in Sweden and Republic of Ireland.

#### Outcomes

##### Primary outcome

Percentage compliance with continence recommendations (Additional file table S1) will be calculated, and a data profile constructed.

#### Secondary outcomes

##### Clinical outcomes

These include number of referrals for specialist continence assessment, incidence of documented incontinence-related dermatitis, urinary tract infections (documented as confirmed by laboratory, confirmed by dipstick or confirmed by symptoms only), and patients' health-related quality of life using I-QoL [45,46] and the EQ-5D [47,48]. The impact of length of stay will be investigated in the analysis, treating length of stay as a co-variant.

##### Process evaluation data

The embedded process evaluation will focus on four areas: facilitation residential programme evaluation; facilitation (i.e., intervention) implementation (i.e., how the intervention plays out in practice); influences on implementation (i.e., enablers and barriers); and the impact of intervention implementation on continence care processes and care home environments.

Qualitative and quantitative data collection methods will be used to strengthen our conclusions through method triangulation. Consistent with a realistic evaluation approach [20,49] our approach to data collection, analysis and integration will be guided by a number of propositions, developed in the initial stages of the study from our conceptual framework, which will be tested throughout the study.

##### Methods of data collection for process evaluation data

Data are being collected through interviews with relevant stakeholders including staff, residents, and next of kin, a questionnaire to assess the context of practice (Alberta Context Tool, ACT), observations and documentary evidence. Our intention is to construct a comprehensive picture of the impact of facilitation on continence practice, nursing home contexts, and residents.

##### The Alberta context tool

ACT has been designed to be a reliable and valid measure of context within complex healthcare settings where care is provided to patients/residents [29]. The ACT is a short questionnaire based on the construct of context (culture, leadership, evaluation) within the PARIHS framework. Additionally, it assesses a number of other concepts that have been found to be important in knowledge translation activity, including structural resources, social capital, organizational slack, and formal interactions. ACT has been designed to be completed by individual care providers, and a number of different versions have been developed for different disciplines and levels of nurses (see [29] for more details). The administration of this instrument will provide us with an assessment of the context in which care is being delivered within the study's nursing homes, and any factors that may explain implementation activity and outcome. Our target sample for the ACT is 30 staff in each home. All nursing staff (licensed practical nurses, registered nurses, and healthcare assistants) who plan and deliver direct care to residents, including continence care, will be asked to complete the questionnaire and return it directly to the research team and/or data entry company. Staff will be identified by the local link person, and the survey administered through the internal postal system. The survey will be administered on three occasions: at baseline, then 12 and 24 months after the intervention. Consent to participate in this part of the study will be assumed if the person decides to complete and return the questionnaire. A second distribution of the questionnaire with a letter reminding staff will be sent to all staff between three and six weeks after the first distribution.

##### Interviews

Semi-structured interviews (telephone and face-to-face) will be conducted with internal and external facilitators, staff, stakeholders, and residents as well as their next of kin during the lifetime of the project. Interviews will be conducted at critical points in the programme pre-, during, and post-intervention. Interviews will focus on the experience of implementation, barriers and facilitators, key events, social, political, and financial aspects of care and service delivery, and more specifically how continence care is delivered. The questions asked in interview will be adapted, depending on the purpose of the interview, and who the stakeholder is.

Data from interviews will enable the capture of intervention specific process information (i.e., about continence care) as well as more general features of the study sites with which to contextualise outcome data from the main intervention project. Interviews will be audio-recorded, and later transcribed.

##### Non-participant observation

We will undertake non-participant observation of care delivery, significant events in the implementation processes and facilitation residential programmes. Non-participant observation will contribute to identifying barriers and facilitators to implementation and practice change, to provide evidence about the role and influence of the facilitators including identifying what are the elements of the role that contribute to 'good enough' facilitation, the reasons for the particular adaptations of the facilitation models to local contexts, and the interactions between facilitation and the context(s) of care.

Observations will be recorded as field notes, including descriptive accounts, and interpretive/reflective comments. Where appropriate and possible, interviews will be timed to follow periods of non-participant observation. Observations will be informed by nine dimensions (space, actors, activities, objects, acts, events, time, goals, and feelings) [50] and the elements contained in the evaluation strands. Anyone who does not wish to be observed will not be part of the observation and no data will be collected relating to them.

##### Routinely collected data

We will gather any available routinely collected local data relevant to the delivery of continence care, and to help us understand the context of care. This may include, for example, an audit of continence care or product use.

##### Documentation

Relevant continence care specific documentation will be collected from each site such as policies, procedures, and guidelines. These should provide useful sources of information about expected continence care practice. Documents will be monitored through from pre- to post- intervention, and any changes made to them noted.

##### Intervention-specific process data

Process data will be collected by facilitators as part of both facilitation interventions, which may include for example the administration of the Context Assessment Index [51], internal facilitators' activity logs, any audits or other evaluations they or the nursing homes conduct during the project, data collected routinely as part of the facilitators' development programmes (e.g., portfolios or reflective diaries, supplies data, policy documents), data collected as a requirement of registration of external audit procedures (appropriate permissions to use these data in anonymised form will be sought).

##### Economic evaluation

The embedded economic evaluation will take a public sector, multi-agency perspective [52,53]. The analysis will be guided methodological best practice for conducting economic evaluations and cost analyses of guideline implementation strategies [54]. The interventions (i.e., facilitation models to enhance compliance with the recommendations) will be fully costed using the finance records plus internal facilitator diaries to record any additional costs that are not fully funded by the study. We will take care to distinguish between research costs and true intervention costs. These facilitation model costs will include residential schools, teleconferencing, travel, salaries, locum support, study time, email, and other support time. In order to find out the ongoing costs of managing continence at study sites, we will collect staff activity and incontinence product use information. Nationally agreed midpoint salaries for the staff grade will be attributed, as appropriate to each participating country. Interviewers will collect costs and types of incontinence products from residential site managers. The time horizon for the trial is two years. All costs will be reported in Euros for the year of study completion. Costs in year two will be discounted at appropriate rates. We will conduct a primary cost-effectiveness analysis to determine cost (in Euros) of achieving various levels of compliance (%) with the recommendations. We will conduct a secondary cost consequence analysis comparing the costs of different facilitation models with a full range of consequences. Amongst these consequences will be self- and proxy-reported health-related quality of life using EQ-5D [55]. Sensitivity analyses will be conducted to see how level of compliance with the recommendations varies according to our assumptions. In our cost effectiveness analysis, we will fully address uncertainty and use cost-effectiveness acceptability curves (CEACs) to convey to policy makers the probability that facilitation models are cost effective at different payer thresholds e.g., £20,000 to 30,000 used by NICE in UK. Subgroup analysis will consider important predictors that may affect quality of life during follow-up, including age, dementia status, or those referred for an incontinence assessment, presence of incontinence related dermatitis, and country of residence.

#### Sample size

##### Power calculation

There is no information available on the current level of compliance with the recommendations, so for the purposes of the power calculation our initial assumption is that there is 50% compliance. It is assumed that in each nursing home 50 patients would be available for assessing compliance with the recommendations. For 90% power to detect if compliance with the recommendations is 15% better in the facilitation arms compared to the standard dissemination arm and allowing for an intracluster correlation of 0.01 and statistical tests carried out at the 5% level, we will, for cluster size 50, require 7 clusters (nursing homes) per intervention arm [56]. Thus 21 clusters in all will be needed. Allowing for potential attrition, this is increased to 8 clusters per intervention arm, so 24 clusters in total. This equates to 6 long term nursing care settings per country with 50 patients per long term care setting.

If compliance with recommendations is lower than 50%, for example 10% (0.1) then for 50 residents per cluster, 4 clusters would be needed per intervention (total 12 clusters). If there were 20 residents per cluster, then 8 clusters per intervention would be needed (total 24), and if 10 residents per cluster then 14 clusters per intervention (total 42) would be needed.

This gives the range of number of clusters potentially needed, given lack of information on current compliance, and allowing for a range of numbers of available residents in each cluster. In this study, it was decided that having 8 clusters per intervention (total 24) would give the study the best chance of detecting a 15% improvement in compliance between the standard dissemination and facilitation arms.

##### Qualitative sample size

Up to five members of nursing staff, five residents, five next of kin and managers and other stakeholders will be interviewed in each site at baseline. Exact numbers will be determined by data saturation and local factors. Further interviews to explore the processes of implementation and its impact will be conducted at points during the study where there have been changes either to continence care or in the context locally at the home, region or nationally.

##### Randomisation

In each country (UK, Sweden, Netherlands, and Republic of Ireland), six sites will be selected which meet the inclusion criteria. These sites will be randomised from a central randomisation point, which will ensure allocation concealment. We will use a stratified random allocation, stratifying by country, and within each strata we will use randomised block of size six. Each site will be randomly allocated to one of three groups: standard dissemination; Type A (technical) facilitation; or Type B (enabling) facilitation. In each country there will be two sites randomly allocated to each arm. The randomisation schedule will be computer generated and prepared by a statistician who is independent of the project team. The country co-ordinators will convey allocation to each site to ensure the research fellows remain blinded.

##### Blinding

There are many challenges of maintaining blinding in this study. However, research fellows collecting outcome and process data will be blind to the random allocation of each site for baseline data collection. From previous experience, we anticipate that the blinding may be inadvertently broken by the sites either during or after baseline data collection. (For example, by referring to external facilitators by name). If and when blinding is broken will be recorded for each site. It is not possible to blind the external facilitators delivering the facilitation programmes as they are delivering the programme because they have specific expertise in that type of facilitation.

##### Timing of data collection

Baseline data will be collected at each site before the intervention. The intervention will take place over 12 months in arm two, and over 24 months in arm three. Outcome data will be collected at 6, 12, 18, and 24 months after the start of the intervention for all groups. This will be concurrent with longitudinal process evaluative data collection.

##### Translations

Interview schedules and recommendations were translated into Dutch and Swedish. These translations were checked by the country co-ordinators. The Quality of Life Scales already had validated Swedish and Dutch versions. The Alberta Context Tool was translated into Swedish and Dutch. A systematic process of translation, back translation, revision, and feasibility assessment based on several years experience and translation into several languages with the ACT was followed.

##### Research fellow training

Research Fellow training was provided before baseline data collection to ensure a common understanding of the process, and reinforced at training sessions throughout the study.

#### Analysis

##### Quantitative analysis

Data will initially be entered onto an excel spreadsheet, uploaded by each country onto a secure central site, and then transferred to SPSS version 18 for analysis. An intention to treat analysis will be carried out on the primary and secondary outcomes. Descriptive statistics will be calculated for all variables of interest. Continuous measures will be summarised using means and standard deviations; categorical variables will be summarized using counts and percentages. Descriptive analyses within and across data sets and within and across sites by country, as well as across countries, will be carried out.

The primary outcome measure, compliance with the recommendations, will be compared at cluster level [56]. Repeated measures analysis of variance will be used to investigate the change in compliance over time by intervention group. Analysis of subgroups and of changes between specific time points can be explored with t-tests or analysis of variance and where appropriate multilevel hierarchical modelling will be used. However, the study is not expected to be sufficiently powered for detailed subgroup analysis.

A Data Management and Monitoring Committee has been set up with agreed terms of reference to review quantitative data management and monitor emerging results.

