**Methods and design:**

Pragmatic randomised controlled trial with three arms (standard dissemination and two different programmes of facilitation), with embedded process and economic evaluation. The primary outcome is compliance with the continence recommendations. Secondary outcomes include proportion of residents with incontinence, incidence of incontinence-related dermatitis, urinary tract infections, and quality of life. Outcomes are assessed at baseline, then at 6, 12, 18, and 24 months after the start of the facilitation interventions. Detailed contextual and process data are collected throughout, using interviews with staff, residents and next of kin, observations, assessment of context using the Alberta Context Tool, and documentary evidence. A realistic evaluation framework is used to develop explanatory theory about what works for whom in what circumstances.

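### The named primary analysis has only time and intervention group; country, which stratified the randomisation, and baseline compliance should enter as covariates

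*Protocol article*

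**What the plan says.** - **Allocation** (Randomisation): "We will use a stratified random allocation, stratifying by country, and within each strata we will use randomised block of size six". There are four countries and two homes per arm in each.
- **Primary comparison** (Quantitative analysis): "The primary outcome measure, compliance with the recommendations, will be compared at cluster level". The method follows: "Repeated measures analysis of variance will be used to investigate the change in compliance over time by intervention group". Time and group are the only factors named.
- **Country in the analysis** (Quantitative analysis): it appears only in the descriptive work, which "within and across sites by country, as well as across countries, will be carried out".
- **Multilevel models** (Quantitative analysis): "where appropriate multilevel hierarchical modelling will be used". This stands in the sentence on subgroups and particular time points, and no covariates are given.
- **Measurement times** (Abstract, Methods and design): "Outcomes are assessed at baseline, then at 6, 12, 18, and 24 months after the start of the facilitation interventions". Timing of data collection adds: "Baseline data will be collected at each site before the intervention".

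The article does not say how baseline compliance enters the repeated measures model.

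**The concern.** The randomisation balances the arms within country, but the named model makes no use of that. If compliance differs between countries, the difference stays in the between-home error of any group main effect. The standard error is then too large and the test rejects too rarely. The third aim of the study expects contextual differences between countries, so this is not far-fetched.

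Baseline compliance is measured in every home before anything is delivered, which makes it a natural covariate. If it is instead one level of the time factor, two tests are available. The group main effect averages in a value that the intervention cannot have changed. The group-by-time test compares changes from baseline, and so carries the full sampling noise of the baseline visit.

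With 24 homes, the precision lost in either way could be recovered from data already collected.

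**Working it through.** **1. The plan's own figure.** Inputs from Power calculation: 50% compliance, 15% better (read as points, so 65%), 90% power, 5% level (two-sided), 50 residents per home, ICC 0.01.

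- Residents per arm, pooled-variance formula without clustering: 226.2, so 227.
- Design effect: 1 + (50 − 1) × 0.01 = 1.49.
- Homes per arm: 227 × 1.49 / 50 = 6.76, so 7. This agrees with the article.
- Power on the effective sample size is 91.1% with 7 homes per arm and 94.2% with 8. No adjustment for country or baseline is assumed.

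**2. Dilution of the group effect.** With baseline as one of five levels and +15 points at each follow-up, the group main effect estimates (0 + 4 × 15)/5 = 12 points, which is 4/5 of 15.

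**3. Change from baseline against adjustment for baseline.** Let τ² be the variance of home compliance that persists across visits (within country), w the visit-specific variance, and ρ = τ²/(τ² + w) the correlation between baseline and one follow-up. For the mean of four follow-ups, per home:

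- change from baseline: w + w/4 = 1.25w;
- adjusted for baseline: τ² + w/4 − τ⁴/(τ² + w) = w(0.25 + ρ);
- ratio, adjusted to change: (0.25 + ρ)/1.25.

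The article does not give ρ. Over an assumed range of 0.1 to 0.6 the ratio runs from 0.35/1.25 = 0.28 to 0.85/1.25 = 0.68. It tends to 1 as ρ tends to 1, where the gain vanishes.

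**4. Country.** A country effect that is the same at every visit cancels from any change, so it costs the group-by-time test nothing. It does not cancel from the group main effect.

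**5. Simulation of the five-occasion analysis.** Set-up: 24 home means, 8 per arm, four countries, +15 points at all follow-ups in both facilitation arms. The ICC is the total, with country inside it. Assumed: 30% of the within-home sampling variance persists between visits, and country holds 0 to 75% of the between-home variance. There were 3,000 runs for power and 2,000 under the null.

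| Total ICC | Group effect, no country | Group-by-time | Mean follow-up with baseline and country |
|---|---|---|---|
| 0.01 | 94–96% | 97–98% | about 100% |
| 0.05 | 47–50% | 98% | above 99% |
| 0.10 | 24–28% | 98–99% | above 99% |

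Rejection rate of the group effect under the null, as the country share rises from 0 to 75%:

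- ICC 0.01: 5.6% falls to 2.0%;
- ICC 0.05: 5.0% falls to 0.8%;
- ICC 0.10: 5.0% falls to 0.6%.

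The group-by-time test kept its nominal level, and its power did not move materially with the country share (97.7% to 97.0% at ICC 0.01). The model with baseline and country rejected in 4.4% to 5.4% of null runs at these three ICCs.

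**6. Other assumptions.** If country variance is added on top of the ICC of 0.01 and ρ runs from 0.1 to 0.6, power is 59–100% for the group effect, 73–99% for group-by-time and 99.9–100% for the adjusted model. With only one arm at +15 points and no persistence of residents' sampling error, group-by-time has 88–90% power and the adjusted model about 100%.

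**7. Degrees of freedom.** 24 homes less 3 arm means leaves 21. Three country indicators and one baseline slope leave 17.

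**The case against.** The strongest reply is that the article is silent on these terms and does not exclude them. A condensed article may leave covariates to a full analysis plan that is not shown here, and baseline as a time level is only the natural reading of a repeated measures analysis over these occasions. A reader might infer that the protocol has decided against country and against baseline adjustment; the text does not say that. But the article does name a method and its factors, and a model with country and baseline is a better choice than the one named.

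The second reply is that the two complaints do not apply to the same test. A reader might infer that leaving out country inflates the error of the planned analysis of change. It does not, because additive country effects cancel there. The country point concerns the group main effect only; for the change test the loss comes from how baseline is handled.

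Third, a simulation of a single follow-up visit gives striking results, for example 66–68% power unadjusted with an assumed country SD of 10 points. Those figures are illustrative at most. They rest on a country variance that the article does not give and do not describe an analysis over five occasions. The correlation is open as well: the article does not say whether the same residents are reassessed, and if many are, the penalty on change scores shrinks.

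Finally, ignoring a stratification factor makes a test conservative, not invalid. That stands.

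**Conclusion.** The point holds as a matter of efficiency. As written, the primary analysis makes no use of the stratification factor and names no adjustment for a baseline measured in every home. In the scenarios examined, the analysis with both matched or beat both repeated measures tests, to within simulation error.

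The size of the gain is not fixed by the document. At its own ICC of 0.01 counted as the total, and with 30% of sampling variance assumed to persist, the loss is about 2 to 6 points of power. Against the change test the gain is negligible when baseline and follow-up are almost perfectly correlated. Against the group main effect it is substantial when homes differ more than the plan assumes.

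A reader might go further and conclude that the trial is underpowered. The documents do not support that: 7 homes per arm reproduces, and 8 give about 94% power with no adjustment.

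**What to change.** State the primary model as a home-level analysis of follow-up compliance at 6, 12, 18 and 24 months, either as repeated outcomes with time in the model or as their mean. Include arm, country (three indicators) and the home's baseline compliance as fixed covariates. Do not use baseline as an outcome level. If the follow-ups are kept as repeated outcomes, an arm-by-time term can still describe how the effect develops, so the interest in change over 24 months is kept.

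The cost is a change of analysis wording and 4 of the 21 between-home residual degrees of freedom, leaving 17. No further data are needed, and the number of homes stays as stated. Any power figure quoted in support should be labelled illustrative, with its assumed country variance and baseline-to-follow-up correlation beside it.

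### The 90% power belongs to a single-occasion facilitation-versus-control comparison, but the named analysis is a three-arm, five-visit repeated measures ANOVA with no primary visit or contrast

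*Protocol article*

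**What the plan says.** **Sample size (Protocol article, Power calculation).** The target is stated as: "For 90% power to detect if compliance with the recommendations is 15% better in the facilitation arms compared to the standard dissemination arm". The inputs are 50 residents per home, an intracluster correlation of 0.01, and "statistical tests carried out at the 5% level". On the control level the article says "our initial assumption is that there is 50% compliance". This gives 7 homes per arm. It continues: "Allowing for potential attrition, this is increased to 8 clusters per intervention arm", or 24 homes in all. No visit and no correlation between visits enters the calculation.

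**Outcome (Primary outcome).** Percentage compliance, with no time point attached.

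**Schedule (Timing of data collection).** Baseline, then months 6, 12, 18 and 24 in every arm. The programmes differ in length: "The intervention will take place over 12 months in arm two, and over 24 months in arm three".

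**Analysis (Quantitative analysis).** Compliance is compared at cluster level. "Repeated measures analysis of variance will be used to investigate the change in compliance over time by intervention group". Changes between particular time points may be explored by t-test or ANOVA, and multilevel models are allowed where appropriate. The same section says: "An intention to treat analysis will be carried out on the primary and secondary outcomes". It gives no rule for a home that misses a visit.

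**The concern.** The sample size section asks one question: does a facilitation arm reach compliance 15 points above control? The analysis section answers another: do the three arms' profiles over five visits differ in any way? A significant interaction could come from Type A, Type B, both, or a difference between the two, and at any visit. A non-significant one does not rule out the 15-point difference that was powered.

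The choice of visit is not neutral. Month 12 is the end of the Type A programme but only halfway through Type B. Month 24 is the end of Type B, and a year after Type A has finished. With no visit fixed in advance, the trial's conclusion on either programme could rest on whichever visit looks best.

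The third issue is missed visits. Classical repeated measures ANOVA uses only units with every visit. A home that leaves late would lose its earlier data too, although the plan expects attrition and promises intention to treat.

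**Working it through.** **1. Reproduce the plan's figure.** Inputs from Power calculation: 50% v 65%, power 90%, 5% level (taken as two-sided; the article does not say), 50 residents per home, ICC 0.01.

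- Residents per arm without clustering, unpooled variance: (1.960 + 1.282)² × (0.50×0.50 + 0.65×0.35) / 0.15² = 223. With pooled variance under the null: 227.
- Design effect: 1 + (50 − 1) × 0.01 = 1.49.
- Homes per arm: 223 × 1.49 / 50 = 6.65, or 227 × 1.49 / 50 = 6.76. Both round up to **7**, as stated.

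The figure is thus reproduced as a two-arm comparison at one occasion.

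**2. Power of that contrast with the 8 homes per arm actually planned.** SE = √[(0.25 + 0.2275) × 1.49 / 50 / 8] = 0.0422, so the non-centrality is 0.15 / 0.0422 = 3.56. With a t reference on 2 × (8 − 1) = 14 df:

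- at 0.05 two-sided: **91.1%**;
- at 0.025: **83.8%**.

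**3. The named test.** Group-by-time numerator df: (3 − 1) × (5 − 1) = 8. Error df: (24 − 3) × 4 = 84. Its power depends on the correlation ρ between one home's percentages at two visits, which the article does not give. As an anchor: if home effects are stable and residents' deviations are independent from visit to visit, ρ = 0.01 / (0.01 + 0.99/50) = 0.34. If half the home variance is visit-specific, ρ = 0.17. If the same residents are measured repeatedly, ρ is likely to be higher.

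The simulation used 20,000 runs per scenario, home-visit variance 0.24 × 1.49 / 50 and equal correlation between all visits. Both facilitation arms have the same effect: either 15 points from month 6, or a linear rise to 15 points at month 24.

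| Assumed ρ | Interaction power, immediate effect | Interaction power, linear rise | One contrast at month 24 |
|---|---|---|---|
| 0 | 69% | 57% | 91% |
| 0.17 | 79% | 67% | 91% |
| 0.34 | 89% | 78% | 91% |
| 0.5 | 97% | 90% | 91% |
| 0.7 | >99% | 99% | 91% |
| 0.9 | >99% | >99% | 91% |

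**4. Why the visit matters.** Suppose Type A peaks at 15 points at month 12 and fades to 5 points by month 24. The Type A contrast at month 24 then has about 20% power at every ρ. This profile is an illustration, not something the article predicts.

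**5. Reading several visits.** Two contrasts with control at four follow-up visits make 8 comparisons; this is a count of what could be tested, not a list in the article. If they were independent, the chance of at least one p < 0.05 under the null would be 1 − 0.95⁸ = 33.7%. Simulated, with the shared control arm: 32%, 31%, 30%, 28%, 23% and 17% at ρ = 0, 0.17, 0.34, 0.5, 0.7 and 0.9. The omnibus interaction test stays at about 5% throughout.

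**6. Missed visits, if only complete homes are used.** Assume each home-visit is missed independently with probability q. A home is complete with probability (1 − q)⁵.

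| Assumed q | Homes complete | Expected of 8 per arm |
|---|---|---|
| 2% | 90% | 7.2 |
| 5% | 77% | 6.2 |
| 10% | 59% | 4.7 |

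Single-contrast t power at 0.05 is 86% with 7 homes per arm, 79% with 6 and 69% with 5.

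**The case against.** Three replies have force.

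*The ANOVA may be the better test.* A reader might infer from the mismatch that the trial is underpowered. The figures do not support that. At ρ = 0.5 with an immediate effect, or at 0.7 and above with either shape, the interaction test has more power than the single-visit contrast. These are long-term care homes, so repeated measurement of the same residents, and hence a high ρ, is plausible. What stands is that the article gives no ρ, so its 90% cannot be attached to this test.

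*No set of visit-wise tests is planned.* A reader might infer that the plan schedules eight unadjusted tests. It does not. It presents time-point comparisons as exploratory and does not list them, and the omnibus test holds its level. What stands is that the omnibus test cannot say whether Type A or Type B beats control, so readers will look to the visits, and nothing says which visit counts.

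*No home is stated to be dropped.* A reader might infer that homes with a missed visit are certain to be excluded. That is a property of the classical method, not a rule in the article. Multilevel models are permitted and can keep incomplete homes. Losing some residents does not remove a home, one spare home per arm was added, and detailed missing-data rules may sit in an analysis plan that is not shown. What stands is a tension between the named method and the intention-to-treat statement.

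**Conclusion.** The point holds as a mismatch between the powered question and the named test, with no primary visit or contrast to join them. Both halves are stated in the article, so this is not merely detail left to an analysis plan.

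Its size: the 90% is replaced by a range of about 57% to over 99% for the interaction test, against about 91% for one contrast at one visit. The false-positive risk of about 17% to 32% arises only if two contrasts are read at all four visits without adjustment. The loss from missed visits arises only if the classical complete-case form of the ANOVA is used.

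The ranges rest on the article's own ICC, home size and effect, and on three assumptions from outside it: ρ from 0 to 0.9, the shape of the effect over time, and the miss rate. It should be corrected, but it does not show that the trial is too small.

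**What to change.** 1. **Name one primary visit.** Month 24 is a natural choice: it is the last visit, the end of the Type B programme and the economic time horizon. The text should say openly that Type A will have ended a year earlier, so its contrast then measures what has been sustained. If the effect at the end of Type A is of interest, make month 12 a labelled secondary contrast.
2. **Name two primary contrasts**, Type A v control and Type B v control, with a stated multiplicity rule such as Holm.
3. **Name the estimating model:** a linear mixed model on all observed home-visit percentages, with a random home effect, visit-by-arm terms, country, baseline compliance and small-sample degrees of freedom. State that homes with a missed visit stay in. Label all other visits secondary.
4. **Restate the power for that test.** With 8 homes of 50 residents per arm, the first Holm step (0.025) has about 84% by an unadjusted t-test on 14 df. This is an approximation to the mixed model, before any gain from adjusting for baseline, and it assumes no home is lost; with 7 homes per arm the same calculation gives about 77%.

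The cost is wording and a lower, but honest, power figure. No extra homes, visits or data are needed to make the change.
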